### Trial design {8}

This study is a parallel-group, two-arm superiority RCT to evaluate the impact of the nutrition therapy Austrian OA Cuisine combined with an evidence-based training programme (GLA:D®) in patients with mild to moderate knee OA in Lower Austria. The treatment combination of the nutrition therapy Austrian OA Cuisine and the GLA:D® training programme is compared with the treatment involving the GLA:D® training programme only.

Participants are informed about all aspects of the study and asked to sign a consent form. Participants are randomised at a 1:1 ratio (see {16a}). Staggered recruitment will be carried out to expand the recruitment phase and to handle all participants’ appointments and trainings more easily.

The duration of the intervention is 9 months. Within this intervention period, the intervention group undergoes the GLA:D® training programme for the first 6 weeks and receives the Austrian OA Cuisine for 9 months. The control group undergoes the GLA:D® training programme for 6 weeks and receives general information regarding a healthy lifestyle. During the 3 months follow-up phase, the intervention group members are expected to implement the Austrian OA Cuisine as well as the exercises of the GLA:D® training programme on their own into their daily life.

## Methods: participants, interventions and outcomes

### Study setting {9}

The study will be implemented in Lower Austria, which is a federal state in north-eastern Austria. Lower Austria is the country’s largest federal state with the second highest number residents (January 2023: 1,718,529 residents). Only Vienna, which is the capital city of Austria, has more residents than Lower Austria [42].

With an arthritis (knee, hip, finger) prevalence of 14.8% of all inhabitants aged at least 15 years, Lower Austria was in fourth place concerning this disease in Austria in 2019 [43].

The trainings and medical examinations are carried out at the David Institute in Krems (located in the centre of Lower Austria and rather close to the capital city Vienna). The David Institute is a regional competence centre for medical training and exercise medicine. Biochemical analyses are carried out at the University of Vienna and the University for Continuing Education Krems. Besides the David Institute, participants can also take part in the trainings at the St. Pölten University of Applied Sciences (also located in the centre of Lower Austria).

### Eligibility criteria {10}

The participants must meet the following inclusion criteria:

Aged ≥ 50 to < 75 yearsA diagnosis of tibiofemoral OA with severity equivalent to Kellgren and Lawrence (K/L) grades 1 to 3

A potential participant is excluded if she/he reports suffering from diabetes mellitus, uncontrolled hypertension, acute/instable neurological or psychiatric diseases (e.g. depression), systematic inflammatory diseases (e.g. rheumatoid arthritis) or alcohol/drug abuse. Further exclusion criteria are obesity classes 2 and 3 (Body Mass Index [BMI] ≥ 35 kg/m^2^) [44] or if participants follow self-reported vegetarian or vegan eating habits.

During the informed-consent process, the prospective participants’ ability to understand the intervention and their German language skills are verified.

Regarding medication and supplementation, the following additional exclusion criteria have been defined:

History of a cortisol therapy in the last 6 weeks prior to the studyTherapy with autologous conditioned plasma in the last 6 weeks prior to the studyInjection of hyaluronic acid in the knee in the last 12 weeks prior to the studyChronic anti-inflammatory medication (e.g. non-steroidal anti-inflammatory drugs)Intake of high-dose nutritional supplements (minimum wash-out of 6 weeks before study start)

The GLA:D® training programme is provided by experienced physiotherapists, who are educated as GLA:D® instructors.

Dietetic group training and individual nutritional counselling are delivered by experienced, registered dietitians of the St. Pölten University of Applied Sciences. The 24-h dietary recalls are administered by a nutritionist or dietitian.

### Who will take informed consent? {26a}

Persons interested in participating can register using an online registration form, by sending an email, or via telephone and the responsible dietitian will contact them.

During the initial appointment, which is conducted online via MS Teams or face to face at the St. Pölten University of Applied Sciences, the dietitian explains the study (background, protocol, different roles, importance of randomisation and adherence) to potential participants and reviews the consent form. Furthermore, the dietitian answers any questions that arise. When the study and its requirements are understood completely and the inclusion and exclusion criteria are met, the informed consent form is signed by the participant and the study coordinator. The participant and the study team each receive a signed version of the informed consent form. All eligible participants must complete the consent procedure before enrolment and randomisation.

### Additional consent provisions for collection and use of participant data and biological specimens {26b}

Independent of this study, the GLA:D® training programme demands the collection of health-related data from all participants for quality control purposes. Therefore, all participants sign the additional consent form of the GLA:D® training programme.

### Interventions

#### Explanation for the choice of comparators {6b}

The research question was based on the PICO (Patient, Intervention, Comparison, Outcome) principle and reads as follows: The effects of the GLA:D® training programme combined with the nutrition therapy Austrian OA Cuisine - compared to the GLA:D® training programme alone - on quality of life in patients with knee osteoarthritis. To answer this research question, a randomised controlled clinical trial is conducted.

Both the intervention group and the control group participate in the GLA:D® training programme, which has already been shown to reduce pain and improve function as well as QL [15]. To examine the synergistic effects, the intervention group receives, in addition to the GLA:D® programme, training and counselling concerning the implementation of the developed nutrition therapy named Austrian OA Cuisine (see {11a}). The control group receives general information about a healthy lifestyle.

#### Intervention description {11a}

The nutrition therapy Austrian OA Cuisine is based on the framework of the New Nordic Diet [34] combined with the food-based dietary guidelines of Austria [45], the guidelines for OA [22, 46], the typical Austrian cuisine (based on standard works of Austrian cookbooks [47, 48], initiatives to promote traditional and regional foods [49–52] and the principles of a sustainable diet [31].

The nutrition therapy consists of dietetic group training and individual nutritional counselling and is realised by an experienced dietitian. There are 4 group trainings covering 2 h each during the first 6 weeks of the intervention at the David Institute in Krems and at the University of Applied Sciences St. Pölten. The curriculum contains:

General information concerning OA and its inflammatory characteristicsThe role of nutrition in the development and progression of OA [53]The principles of the Austrian OA Cuisine (e.g. largely plant-based, rich in n-3 fatty acids)The practical implementation in daily life (including a recipe booklet)A tasting of different dishes and practical exercises to increase food literacy (e.g. adapting own recipes) [54]Strategies for self-management, self-motivation, self-control and goal-setting [55]

The concept of the Austrian OA Cuisine provides adequate intake of energy and nutrients for the age group over 51 years [56], which is the age group most affected by OA. Besides, it takes the sustainability aspect into account - e.g. by giving preference to regional and seasonal products. The developed diet meets the recommendations for an anti-inflammatory diet [57].

After the end of group training, a comprehensive individual counselling will be provided once a month until 9 months after the study start, either face to face, by telephone, or virtually (MS Teams). The individual counselling consolidates the knowledge and competences and also monitors and motivates participants to keep implementing the therapeutic diet.

After 9 months of nutrition therapy, a follow-up of 3 months will be implemented. During this time, participants should continue to implement the Austrian OA Cuisine on their own.

The GLA:D® training programme consists of two patient education sessions (approx. 1.5 h per session) and two supervised, group-based exercise therapy sessions (approx. 1 h per session) per week over the first 6 weeks of the intervention. The education sessions include information about OA, its symptoms, treatment options and self-management strategies. The group training is based on the NEMEX programme [58] and includes exercises to strengthen hip and knee muscles as well as neuromuscular exercises to improve joint control and stability. Although it is a standardised programme, the exercises can be individualised and adapted to the patients’ needs [13, 59]. The education and training sessions take place at the David Institute Krems and the St. Pölten University of Applied Sciences.

### Criteria for discontinuing or modifying allocated interventions {11b}

Participants can revoke their willingness to participate at any time, even without giving reasons, and withdraw from the clinical study without any disadvantages for their further medical care.

The principal investigator may terminate a participation in the study prematurely without obtaining the participants' consent beforehand. Reasons for this include:

Participants do not longer meet the inclusion criteria of the clinical study.The treating physician comes to the conclusion that continued participation in the clinical study is not in the participants' best interest.The study coordinator decides to terminate the entire clinical study, or to terminate only one subject’s participation prematurely.

Furthermore, participants must attend at least three out of four dietetic group training sessions and eight out of twelve GLA:D® training programme sessions. If a participant cannot meet this quota, he/she is excluded from the study.

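### The attendance quota in {11b} removes people from the study rather than from the intervention, and its dietetic half can remove intervention-arm participants only, so T4 KOOS-QL is probably lost for some of the randomised people the ITT analysis needs

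*Protocol article*

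**What the plan says.** Under {11b}, "participants must attend at least three out of four dietetic group training sessions and eight out of twelve GLA:D® training programme sessions". The consequence follows directly: "If a participant cannot meet this quota, he/she is excluded from the study". The same section gives further grounds on which the principal investigator may end participation, among them "The study coordinator decides to terminate the entire clinical study, or to terminate only one subject’s participation prematurely".

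The two halves of the quota do not apply to the same people. GLA:D is given to both arms, as "two supervised, group-based exercise therapy sessions (approx. 1 h per session) per week over the first 6 weeks of the intervention" ({11a}). The dietetic sessions belong to the nutrition therapy, which only the intervention group receives. For the comparator, {6b} says "The control group receives general information about a healthy lifestyle". On timing, {11a} states "There are 4 group trainings covering 2 h each during the first 6 weeks of the intervention".

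For the analysis, {20a} centres on T0 against T4 (12 months), and {20c} commits to ITT for nonadherence and to multiple imputation for missing data. The primary outcome is KOOS-QL ({12}), completed on laptops at the measurement site ({18a}). Neither {11b} nor the retention section {18b} says that people excluded under the quota continue to be measured.

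**The concern.** SPIRIT item {11b} is about stopping or modifying the allocated intervention. Here the rule ends study participation. It acts after randomisation, on behaviour that the allocated treatment itself creates, and one half of it has no counterpart in control. The people it removes are the least adherent, which is the group an ITT analysis exists to keep.

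The quota is settled by about week 6, so an excluded participant contributes KOOS at T0, or at T0 and T1 at most. The mixed model and the imputation must then fill in T4 on the assumption that poor attenders resemble attenders with the same recorded data. If poor attenders would have done worse for reasons that were not recorded, the T4 comparison tilts towards the intervention.

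**Working it through.** **Inputs from the protocol article.** Quota of 3 of 4 and 8 of 12 sessions ({11b}); 30 per arm included, 25 required, SD 15, MIC 8 to 10 points ({14}); 5% significance level ({20a}), taken as two-sided. The article gives no attendance rate, so there is no figure of its own to reproduce. The nearest is the drop-out allowance: 30 − 25 = 5 losses per arm.

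**Assumptions.** Per-session attendance probability p, the same for both session types; correlations as stated below.

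**Step 1: exclusions with independent sessions.**
- a = P(fewer than 3 of 4 attended); b = P(fewer than 8 of 12 attended), both binomial.
- Intervention arm: 1 − (1 − a)(1 − b). Control: b. Multiply each by 30.
- Example, p = 0.90: a = 1 − (4 × 0.9³ × 0.1 + 0.9⁴) = 1 − 0.9477 = 0.0523; b = 0.0043; intervention 1 − 0.9477 × 0.9957 = 0.0564.

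| p | a | b | Intervention, of 30 | Control, of 30 |
|---|---|---|---|---|
| 0.95 | 0.0140 | 0.0002 | 0.4 | 0.0 |
| 0.90 | 0.0523 | 0.0043 | 1.7 | 0.1 |
| 0.85 | 0.1095 | 0.0239 | 3.9 | 0.7 |
| 0.80 | 0.1808 | 0.0726 | 7.2 | 2.2 |

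At 80% the quota alone uses more than the 5 losses allowed in the intervention arm.

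**Step 2: attendance clustered by person.** Let each person's p follow a beta distribution with the given mean and within-person correlation r (parameters mean × (1/r − 1) and (1 − mean) × (1/r − 1)), shared across both session types. Average a and b over that distribution.

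| Mean p | r = 0.3: intervention v control (difference) | r = 0.5: intervention v control (difference) |
|---|---|---|
| 0.90 | 4.1 v 2.7 (1.4) | 4.1 v 3.2 (0.9) |
| 0.85 | 6.4 v 4.4 (2.0) | 6.1 v 4.9 (1.2) |
| 0.80 | 8.7 v 6.3 (2.4) | 8.2 v 6.7 (1.5) |

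Clustering narrows the gap between arms to about 1 to 2.4 of 30, but control then also loses about 3 to 7.

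**Step 3: effect on the T4 comparison.** Simulated trials with no true effect: 30 v 30, SD 15, T0–T4 correlation 0.3 to 0.7, T4 compared with adjustment for T0. The participants ranked lowest on an unrecorded factor are removed. The removal counts are the Step 1 results for 90%, 85% and 80%, rounded. c is the correlation of that factor with the part of T4 that T0 does not predict.

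| Removed (intervention v control) | c = 0.3: shift in points; error | c = 0.5: shift in points; error |
|---|---|---|
| 2 v 0 | 0.44–0.56; 5.3–5.6% | 0.71–0.96; 5.9–6.0% |
| 4 v 1 | 0.54–0.72; 5.5–5.6% | 0.91–1.21; 6.6–6.7% |
| 7 v 2 | 0.82–1.13; 5.9–6.2% | 1.36–1.83; 7.9–8.4% |

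With c = 0 there is no shift beyond simulation noise (at most 0.11 points under explicit multiple imputation on arm and T0) and error stays near 5%.

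**Step 4: would a T1 KOOS value rescue the imputation?** With equal correlation ρ between visits, the residual SD of T4 shrinks by √(1 − 2ρ²/(1 + ρ)) / √(1 − ρ²) = 0.97, 0.94 and 0.91 for ρ = 0.3, 0.5 and 0.7. The shift falls by 3 to 9%.

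**The case against.** **Loss of T4 is inferred.** The quota stands under a heading about interventions, and {20c} provides separately for ITT and imputation. The two can be reconciled if excluded people stay in the analysis set with T4 imputed. A reader might infer that the trial gives up ITT or plans a completers-only analysis, and the document does not support that. What stands is that the wording ends study participation and nothing keeps measurement going. If follow-up is intended, the sentence says the opposite.

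**The arm difference depends on independence.** Someone who stops coming usually misses GLA:D too and is then excluded in either arm. This is right, and Step 2 shows the gap shrinking. The total loss of data does not shrink, and the 7 v 2 case lies near the extreme of the range for imbalance.

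**Attendance may be high.** Participants are briefed before consent, reminded, compensated and treated free of charge ({11c}). At 95% with independent sessions the rule removes almost no one.

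**The bias model is unfavourable.** It removes strictly the lowest-ranked people on a wholly unrecorded factor and imputes from arm and T0 KOOS. The trial also records functional tests, other KOOS subscales, self-rated health and pain, and physical activity, all of which imputation could use. This stands, so the shifts are best read as upper-range illustrations.

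**Other termination grounds.** One ground reads "Participants do not longer meet the inclusion criteria of the clinical study". Set beside the age limit and "severity equivalent to Kellgren and Lawrence (K/L) grades 1 to 3", a reader might infer that anyone who turns 75 or progresses beyond grade 3 must leave. The document does not support this: the ground is discretionary and applies equally to both arms, and {12} lists no follow-up imaging. Nor should the quota be read literally as excluding every control for attending no dietetic sessions; the sensible reading applies that half to the intervention arm.

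**Conclusion.** The point holds as a minor one. As worded, {11b} takes poor attenders out of the study by about week 6. Half of the rule can bind in one arm only, and T4 KOOS-QL is then likely not collected for people the ITT analysis must include.

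The number affected rests on assumed attendance: from almost none at 95% with independent sessions to about 7 or 9 of 30 in the intervention arm at 80%. The shift rests on assumed correlations. It is zero if recorded data explain the removal, and about 0.4 to 1.8 points otherwise, which is less than a quarter of the 8-point MIC (2 points). A claim of serious bias is not supported. The case for changing the text is that the risk is avoidable: following these participants to T4 makes the untestable assumption unnecessary for them.

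**What to change.** In {11b}, make the attendance quota, and any individual termination by the investigator or coordinator, a reason to stop the intervention only. State that these participants stay in KOOS collection to T4 and in the ITT set unless they withdraw consent. Log reason, date and arm for each case so that the imputation model can use them. Use the quota only to define a per-protocol set. Termination of the entire study lies outside this change.

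The cost is two sentences, a short log, and the remaining KOOS assessments for a few stopped participants. These can be done at site visits or through the existing personalised questionnaire link ({19}), with the mode recorded. No extra patients are needed.

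Recruitment ended in January 2024, so new wording may come too late to recover T4 values. In that case, report quota exclusions by arm, keep those people in the ITT set, and add a sensitivity analysis that does not assume they resemble attenders.

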### Strategies to improve adherence to interventions {11c}

At the first appointment prior to the start of the study, the potential participants receive a detailed description of the study (background, randomisation, intervention, results, etc.) to be sure that they have understood everything correctly before giving their consent to participate in the study (see ‘Who will take informed consent? {26a}’). This initial appointment is conducted by the dietitian who has the most contact with the participants during the study. This supports personal contact and adequate relationships from the beginning.

Throughout the study, the central study staff members - mainly the dietitian - maintain close contact to further strengthen human relationships. The participants are reminded about all appointments via text message 1 week beforehand. The data collection at the different measurement times is well organised with time slots to reduce waiting times for the participants. During the initial 6-week group training (GLA:D® training programme and dietetic group training), the participants build intensive relationships with each other and with the central study staff members due to the intensity of the programme. Through the monthly performed 24-h dietary recalls (see {12}) and the subsequent individual nutritional counselling, the participants in the intervention group are encouraged to continue implementing the recommendations of the Austrian OA Cuisine after the end of the group phase [60].

Throughout the course of the study, participants receive selected interim results (for example, the body composition measurement) to promote motivation. After the study is finished, they will also be provided their data from the biochemical measurements, if they wish so.

Participants receive a financial compensation and a goodie bag with highly relevant food groups of the Austrian OA Cuisine - mainly organic and locally produced vegetable oils and nuts. Additionally, participants take part in the evidence-based GLA:D® training programme guided by experienced GLA:D® physiotherapists free of charge. Regularly, the costs of physiotherapy are not fully covered by insurance in Austria. As a central component of the intervention, the intervention group members participate in holistic nutrition therapy counselled by an experienced dietitian, also without additional costs. Besides, the control group has the possibility to discuss their eating habits and biochemical data with a dietitian after the study is finished.

### Relevant concomitant care permitted or prohibited during the trial {11d}

Participants are instructed not to take high-dose dietary supplements during the study (e.g. vitamin supplements that exceed the reference values [56] for the nutrient intake). Any changes in medication or supplementation are queried at the various data collection points.

#### Provisions for post-trial care {30}

Study participation entails only minimal risk because nutrition therapy [29, 61] - in this case, the Austrian OA Cuisine - and the GLA:D® training programme [13] are associated with extremely low health risks. Therefore, no special provisions for post-study care are included.

### Outcomes {12}

Data are collected five times over a period of 12 months: at baseline (T0), 6 weeks after the start of the intervention (T1; T0 + 6 weeks), 3 months after the start of the intervention (T2; T0 + 3 months), 9 months after the start of the intervention (T3; T0 + 9 months) and after the follow-up period (T4; T0 + 12 months), including the assessment of blood-based biochemical, anthropometric and behavioural parameters at four data collection points (T0, T2, T3 and T4). The collection of demographic and anamnestic data and the execution of the functional tests take place at all five data collection points.

The primary outcome is the quality of life subscale (QL) of the Knee Injury and Osteoarthritis Outcome Score (KOOS) [62]. The KOOS is used to assess the joint function and patients’ opinion about their knee and associated problems and is a valid and reliable tool compared to others in several studies [62]. The KOOS score for knee-related quality of life (QL) is one of five subscales of the KOOS questionnaire. The QL score is calculated based on four 5-point Likert scale questions, in which each question is assigned a score between 0 and 4. According to the standardised score calculation (www.koos.nu), the mean of the observed items is divided by 4, multiplied by 100 and finally subtracted from 100. A QL score of 100 indicates no symptoms, while a score of 0 means extreme symptoms. The KOOS is valid and reliable and was compared to other instruments in several studies [62].

To evaluate the symptoms of the knee OA and associated problems, the following parameters are analysed:

Further KOOS subscales collect the participants' opinion about their knee pain (Pain), knee function in daily living (ADL), knee function in sport and recreation (Sport/Rec) and other knee-associated symptoms (Symptoms). The latter is relevant for testing H2. Equally to the KOOS subscale QL, each subscore is calculated based on 5-point Likert scale questions, where each question is assigned a score from 0 to 4. Following the standard procedure for the subscore calculation, the mean of the subscore questions is divided by 4, multiplied by 100 and finally subtracted from 100. A subscore of 100 indicates no symptoms, while a score of 0 points to extreme symptoms.To evaluate the functional status of the participants' knee, the 40-m fast-paced walk test (40 MFPWT) and the 30-s chair stand test (30 SCST) are performed. The 40 MFPWT is a valid and reliable tool to measure gait speed and to monitor changes in knee OA patients’ physical function over time [63]. The 30 SCST is a valid and reliable tool to measure lower limb strength in patients with knee OA [64].

The following nutritional parameters are used as the basis for testing the third hypothesis:

Anthropometrical parameters:Body height [cm], body weight [kg] and body fat [%] as measured using Seca mBCA 555. The device measures body weight with a scale, body height with ultrasound length measurement and body composition by the voltage drop of the alternating current in one stepWaist circumference [cm] to calculate the waist-to-height ratio as measured using an ergonomic, stepless and extendible measuring tape

Biochemical parameters:Lipide profile (plasma α-linolenic acid, plasma linoleic acid, plasma total polyunsaturated fatty acids, plasma Ω6:Ω3 ratio), measured as described in [65];Carotenoids (α- and β-carotene, lutein, lycopene), measured as described in [66, 67] and;Vitamins D [68] and K, measured as described [66].

Behavioural parameters:Dietary behaviour is measured using an adapted version of the Vienna Food Record (VFR), which is a paper-based prospective food record and can be completed without an interview or oral instruction. The VFR consists of 182 food items which meet the requirements of Austrian adults [69]. For this study, adaptations to assess fat quality (fat fish, vegetable oils, nuts and seeds) more precisely were implemented. To support participants in answering the VRF, an additional booklet with real portion size pictures corresponding to the food items are provided to the participants.

Additionally, the oxidative stress and inflammatory status are determined as secondary outcomes based on the following biochemical parameters:

Oxidative stress parameters (ferric reducing ability potential, malondialdehyde, oxidised and reduced glutathione, damage to desoxyribonucleic acid), measured as previously described [70].Inflammation biomarkers (C-reactive protein, interleukins (IL)-1β, IL-6, IL-18, tumour necrosis factor alpha, matrix metalloproteinase (MMP)-3), measured by multiplex assays as described previously [71].

In addition to the outcome parameters, the following demographic and anamnestic data are collected:

Sex, gender, employment status, residence, number of people in the household, income, immigration background [72]Consumption of alcohol and smoking behaviourSleep qualityClinical information (menopausal status, regular intake of supplements and drugs, medical history, joint complaints, sick leave)Actual self-perceived health status and painPhysical activity level at work, leisure time activitiesThe general physical activity level is assessed using the ‘International Physical Activity Questionnaire Short Form’ (IPAQ-SF) [73]: The IPAQ-SF asks seven questions to assess ‘vigorous-intensity’ and ‘moderate-intensity’ physical activity as well as ‘walking’ and ‘sitting’. Participants indicate the time in minutes or hours for each activity level. Based on this information, three levels of physical activity (low, moderate, high) are calculated and expressed in the metabolic equivalent of task (MET) minutes per week.Feedback on the participants’ satisfaction with the GLA:D® training programme will be collected at T1 and T4 by using a visual analogue scale.

Besides these measurement appointments, participants take part in monthly 24-h dietary recalls via telephone, except for the first, which is conducted in person at the second measurement point (T1). Interviews are performed by trained project staff in a structured manner based on the framework of the multiple-pass method [74–76]. Except for one 24-h dietary recall, which gathers data on weekend eating behaviour, the other seven 24-h dietary recalls collect data on eating behaviour from Monday to Thursday. To reduce bias, participants know only the calendar week for the 24-h dietary recalls but not the exact day. All 24-h dietary recalls are analysed using the programme nut.s nutritional software (https://www.nutritional-software.at) in its latest version (April 2022) [77].

Furthermore, qualitative data are collected 7 months after each intervention round has started. This will be done via three focus groups with intervention group participants. It will be conducted to analyse the acceptance of the Austrian OA Cuisine and identify perceived social and cultural barriers as well as supportive factors for its integration into daily life. By taking these data into account, a more holistic understanding of the success of the implementation of the nutrition therapy will be possible. Provisional topics used to guide the focus groups will be developed in advance. The focus groups will be managed by a dietitian of the study staff. The dietitian will be responsible for recording, documenting and creating a summary analysis.

